## Abstract

**Background:**

Postoperative delirium is a common disorder in older adults that is associated with higher morbidity and mortality, prolonged cognitive impairment, development of dementia, higher institutionalization rates, and rising healthcare costs. The probability of delirium after surgery increases with patients’ age, with pre-existing cognitive impairment, and with comorbidities, and its diagnosis and treatment is dependent on the knowledge of diagnostic criteria, risk factors, and treatment options of the medical staff. In this study, we will investigate whether a cross-sectoral and multimodal intervention for preventing delirium can reduce the prevalence of delirium and postoperative cognitive decline (POCD) in patients older than 70 years undergoing elective surgery. Additionally, we will analyze whether the intervention is cost-effective.

**Methods:**

The study will be conducted at five medical centers (with two or three surgical departments each) in the southwest of Germany. The study employs a stepped-wedge design with cluster randomization of the medical centers. Measurements are performed at six consecutive points: preadmission, preoperative, and postoperative with daily delirium screening up to day 7 and POCD evaluations at 2, 6, and 12 months after surgery. Recruitment goals are to enroll 1500 patients older than 70 years undergoing elective operative procedures (cardiac, thoracic, vascular, proximal big joints and spine, genitourinary, gastrointestinal, and general elective surgery procedures).

**Discussion:**

Results of the trial should form the basis of future standards for preventing delirium and POCD in surgical wards. Key aims are the improvement of patient safety and quality of life, as well as the reduction of the long-term risk of conversion to dementia. Furthermore, from an economic perspective, we expect benefits and decreased costs for hospitals, patients, and healthcare insurances.

**Trial registration:**

German Clinical Trials Register, DRKS00013311. Registered on 10 November 2017.

**Electronic supplementary material:**

The online version of this article (10.1186/s13063-018-3148-8) contains supplementary material, which is available to authorized users.

## Background

Delirium is associated with increased morbidity and mortality, cognitive impairment, dementia, and higher institutionalization rates [1]. The incidence of postoperative delirium (POD) depends on factors predisposing to delirium such as age, the presence of brain damage, dementia, deficits in cognitive, sensory, or mobility functions, multiple comorbidities, polypharmacy, and frailty [2]. Early indicators of cognitive deficits, including hyposmia [3], sleep disorders [4, 5], and subjective memory impairment [6, 7], are also relevant risk factors for delirium. The perioperative phase is a major trigger of postoperative delirium because of the administration of anesthesia, the surgical procedures, and other factors related to the operation itself, such as pain and immunological activation [2]. Postoperative cognitive dysfunction (POCD) often appears after POD [8, 9] and has been studied in relation to the preoperative status in order to measure the delirium’s impact, particularly on the risk of developing dementia [10], and in order to estimate the related health costs. POD and POCD are associated with higher mortality and postoperative complications (such as infections, falls, decubitus ulcers, incontinence) [9], with prolonged hospital stays [11], with the need for longer/extended intensive care and therapy and higher nursing workload burden [12], and with increased costs for both hospitals and healthcare insurance providers [2, 13].

Delirium is a healthcare quality indicator in older adults, and therefore delirium prevention is an essential parameter for patients’ safety [14, 15]. The incidence of delirium and its severity and duration can be significantly decreased and may be stratified by taking delirium risk factors into account [16]. Current guidelines for POD management [17] emphasize the importance of delirium prevention. A multimodal nonpharmacological approach [14, 18] is considered the best pathway [16, 19]. In a meta-analysis [20], this approach reduced the delirium risk by 53% (95% CI, 0.38 to 0.58) when comparing intervention and control groups.

For elective surgery, it is possible to implement a preadmission delirium prevention plan [21], adapting care to the patient’s age and delirium risk. However, surgical centers typically do not implement preadmission procedures for delirium risk assessment, and recommended interventions for the management of delirium are not standardized.

In this study, we will develop a cross-sectoral and “best practice” multimodal delirium prevention approach in five medical centers. The proposed multisectoral model for delirium prevention integrates and builds upon several multimodal admission models [16] with preadmission risk reduction counseling (“prehabilitation”), perioperative monitoring [22], and training based on international guides [17, 23] of multidisciplinary patient care providers, including operation room personnel, service staff, and families. The study will optimize delirium assessment, establish a cross-sectoral intervention bundle for preventing delirium, and evaluate the effectiveness and cost-efficiency of this all-encompassing approach. To this end, evidence-based delirium diagnoses, neuropsychological tests, and multimodal multiprofessional interventions will be implemented. Follow-up POCD evaluations will be performed 2, 6, and 12 months after surgery. Furthermore, relatives will be asked about their care burden, and a cross-sectoral analysis of the perioperative patient pathway will be performed.

The project, recruiting a total of 1500 patients, has the following objectives:The evaluation of the perioperative delirium prevalence with the I-Confusion Assessment Method-based scoring system for delirium diagnosis and delirium severity (I-CAM-S) [9], which is used for the first time in a large multicenter German sample.The implementation of a multisector, individualized, multiprofessional and multimodal delirium and POCD prevention program.The evaluation of the prevalence of POCD at 2 and 6 months after surgery, and the persistence of POCD after 12 months.The evaluation of changes in medication during the pre-admission and perioperative phases, especially with respect to avoidance of anticholinergic drugs and other pharmacologic agents associated with delirium.The evaluation of the care burden of the patients’ relatives.The economic evaluation of the multimodal intervention, studying its cost-effectiveness. From the point of view of the hospital departments, initial hospital costs will be evaluated. From the point of view of the health and care insurance company Allgemeine Ortskrankenkasse (AOK) Baden-Württemberg (Germany), inpatient and outpatient costs during the 12 months before and after the surgery will be analyzed in relation to outcome differences.

## Methods

### Design

We have designed a cross-sectoral longitudinal study that aims to include 1500 patients undergoing elective surgery. The study employs a stepped-wedge design with cluster randomization of five medical centers. The study will have seven periods, each lasting 12 weeks (see Fig. 1). The study will evaluate an all-encompassing “best practice” multimodal intervention for preventing delirium and POCD that includes six consecutive measurement points: preadmission, preoperative, and postoperative including daily delirium screening for 7 days after surgery and 2, 6, and 12 months after surgery. We aim to show that: the cross-sectoral multimodal and multidisciplinary intervention reduces the delirium rate by at least 40% compared with treatment as usual; the cross-sectoral multimodal and multidisciplinary intervention reduces the rate of postoperative cognitive decline by at least 20% compared with treatment as usual; and the cross-sectoral intervention, including the team training and the modules for nonpharmacological prevention, is cost-effective and therefore the improvement in quality of life imposes no additional costs because the care needs of the patients and caregivers are lower than with the standard treatment.

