#### Sample size

The power analysis for the primary outcome of delirium prevalence assumes a reduction in the outcome from 25% to 15% [20] as a result of the intervention. A conventional analysis to detect differences in proportions (delirium rate) between the intervention and control groups, using Fisher’s exact test, results in a total of 514 patients with a 1:1 randomization, given a power of 1 – β = 0.80 and an α error of 5%. Using the adjustment form proposed by Woertman et al. [67] with five crosspoints in a stepped-wedge design, with a maximum of 50 patients per cluster per period and an intracluster correlation of 0.01, leads to a correction factor for the stepped-wedge design of KF = 2.63, and therefore a number of 514 × 2.63 = 1351 patients. Assuming a dropout rate of 15%, this leads to a total requirement for about 750 patients per arm. The minimum number of clusters is given by the ratio of the total number of patients to the product between the number of crossing points and the patients per cluster per period, and is 15.

For the secondary outcomes, a reduction of the persistent cognitive deficit from 20% to 10% results in 428 patients using the conventional analysis with Fisher’s exact test and a 1:1 randomization, a power of 1 – β = 0.80, and an α error of 5%, which after the design correction leads to a requirement of 1079 patients.

Thus, the planned sample size is of at most 1500 patients (see Fig. 1 with the numbers per period). Furthermore, relatives of the patients will be asked about the burden of caring and the cognitive status of the patients.

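### The POCD aim is a reduction of at least 20%, but the cognitive outcome is sized for 20% to 10% (50% relative), and its corrected total of 1079 does not follow from the stated factor

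*Protocol article*

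**What the plan says.** The Design section lists paired aims. For delirium, the intervention "reduces the delirium rate by at least 40% compared with treatment as usual". For cognition, "the cross-sectoral multimodal and multidisciplinary intervention reduces the rate of postoperative cognitive decline by at least 20% compared with treatment as usual".

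The Sample size section plans delirium at 25% to 15%. It obtains 514 patients, multiplies by a stepped-wedge correction factor of 2.63 to reach 1351, and allows for 15% dropout to arrive at about 750 per arm. For the secondary outcome it states that "a reduction of the persistent cognitive deficit from 20% to 10% results in 428 patients". This is again a Fisher calculation with equal allocation, 80% power and a 5% error rate. The corrected figure follows in the same sentence: "which after the design correction leads to a requirement of 1079 patients". It gives no second correction factor and mentions no dropout for this outcome. The planned total is at most 1500.

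The study objectives (end of Background) and the Outcome assessment section separate the prevalence of POCD at 2 and 6 months from its persistence at 12 months.

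**The concern.** The two sections plan for different effects. For delirium, the aim and the planning rates agree. For cognition, the planning rates describe a reduction 2.5 times the smallest one named in the aim (50% against 20%). The outcome also changes name between the sections, so it is unclear whether the power statement concerns the same endpoint as the aim.

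A reader of the Sample size section would take the second aim to be powered. A non-significant POCD result could then be read as evidence against a 20% reduction, although nothing in the document shows that the trial could detect one.

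The corrected total of 1079 also does not follow from the only factor given.

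**Working it through.** **Inputs.** From Design: aims of 40% (delirium) and 20% (POCD). From Sample size: 25% to 15%; 20% to 10%; 428; 1079; factor 2.63; dropout 15%; at most 1500 patients. Sidedness is not stated. I assume two-sided, and that reproduces 428.

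**Scale of the aims.** Delirium: (25 − 15)/25 = 40%, so the aim matches the planning rates only as a relative reduction. Cognition: (20 − 10)/20 = 50% relative, or 10 points absolute. Read as absolute points, the 20% aim would mean 20% to 0%, which does not fit either.

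**The plan's own figures.**
- Exact two-sided Fisher power for 20% vs 10%: 214 per arm gives 0.801 and is the smallest size reaching 0.80. The total of 428 reproduces.
- Primary outcome: 514 × 2.63 = 1351.8. The stated 1351 reproduces.
- Cognitive outcome: 428 × 2.63 = 1125.6, i.e. 1126. The stated 1079 does not reproduce; it is 47 too low.
- Implied factor: 1079/428 = 2.52. Working backwards, 1079/2.63 = 410, and 205 per arm has Fisher power of only 0.780.
- With 15% dropout: 1126/0.85 = 1324.7, i.e. 1325.

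**A 20% relative reduction at an assumed base rate of 20% (20% to 16%).** Per arm, by the normal approximation:

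n = [1.96·√(2·0.18·0.82) + 0.842·√(0.20·0.80 + 0.16·0.84)]² / 0.04² = 1447, total 2894.

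With continuity correction, (n/4)·[1 + √(1 + 4/(n·0.04))]² = 1497, total 2994.

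After the factor: 2894 × 2.63 = 7,611 and 2994 × 2.63 = 7,874.

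**Power for 20% to 16%.** Effective patients per arm = N/(2 × 2.63).
- N = 1500: 285 per arm, power 0.236.
- N = 1275 (1500 less 15%): 242 per arm, power 0.208.
- For comparison, the same approximation for 20% to 10% gives 0.92 and 0.87.

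**Dependence on the base rate** (20% relative reduction, continuity-corrected):

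| Base rate | Before factor | × 2.63 | with 15% dropout |
|---|---|---|---|
| 10% | 6,626 | 17,426 | 20,502 |
| 20% | 2,994 | 7,874 | 9,264 |
| 30% | 1,784 | 4,692 | 5,520 |
| 40% | 1,178 | 3,098 | 3,645 |
| 50% | 816 | 2,146 | 2,525 |
| 60% | 574 | 1,510 | 1,777 |
| 65% | 480 | 1,262 | 1,485 |
| 70% | 400 | 1,052 | 1,238 |

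Before dropout the need drops below 1500 just above a 60% base rate; with dropout, at about 65%.

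**The case against.** **The endpoints may differ.** Cognitive decline in the aim may mean POCD at 2 and 6 months, and persistent deficit may mean the 12-month outcome. The 20% base rate would then belong to another endpoint. This stands as a limit on the figures: 7,600 to 7,870 patients and 21% to 24% power hold only if 20% is the base rate. A much higher rate is conceivable. The Outcome assessment section counts a deficit when any one test reaches a 0.5 SD threshold. Read as 0.5 SD below the norm (an assumption), one test alone would flag about 31% of a normative population. Any of four independent tests would flag 1 − 0.69⁴, about 77%. A reader might therefore infer that the trial is shown to be underpowered for its POCD aim; the documents do not establish that. But if the endpoints do differ, the aim has no power calculation at all.

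**A 50% reduction also satisfies 'at least 20%'.** True, so the two sections are not a strict logical contradiction. Still, the delirium calculation uses the smallest reduction named in its aim, and the cognitive one does not. One might go further and read 'at least' as a claim that smaller effects must be excluded, which would rarely succeed if the truth equalled 20%. The document states no such margin test and plans to detect a difference, so that reading is not supported.

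**The 1079 has no consequence and may rest on another factor.** The first part stands: the total of 1500 comes from the primary outcome. The second is possible, but the text gives only 2.63.

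**Conclusion.** The point holds. The aim (20%) and the planning effect (50% relative) for cognition do not agree, the endpoint is named differently in the two places, and no stated power supports the 20% aim. This rests on reading 20% as relative, which the delirium pair supports.

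The size of the shortfall is conditional. At the document's own 20% rate, power is about one in five to one in four. The requirement exceeds 1500 across base rates from 10% to 60% and, with dropout, comes within 1500 only from about 65%.

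The 1079 is inconsistent with the stated factor by 47 patients. It would be wrong to infer that the planned sample size must change: 1126 evaluable or 1325 enrolled both lie within 1500, and 1500 less 15% leaves 1275, above 1126. The defect lies in what the document says the trial can show on POCD.

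**What to change.** 1. In Design and Sample size, use one name for the cognitive endpoint and give its time point.
2. State that the trial is planned to detect 20% to 10% (50% relative) on that endpoint. Say openly that, at a 20% base rate, power for a 20% relative reduction is about 21% to 24%. If another base rate is expected, state it and give the power that follows.
3. Replace 1079 with 1126 (1325 with 15% dropout), or state the different correction factor used and why it applies.

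The cost is text only: the design and the planned 1500 are unaffected. Recruitment has begun, so a reworded aim should be dated and reported through the route that the Ethics section sets for relevant changes, including the registry.

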**Fig. 1 Fig1:**
[figure not shown]
Timeline and randomization

The study strategy is registered, constructed, and presented according to the recommendations of the Standard Protocol Items: Recommendations for Interventional Trials (SPIRIT) [24, 25] (see Additional file 1: SPIRIT checklist). The items from the World Health Organization Trial Registration Data Set are presented in Table 1.

**Table 1 Tab1:** Items from the World Health Organization Trial Registration Data Set

1	Primary registry and trial-identifying number: DRKS-ID, DRKS00013311
2	Date of registration in primary registry: 10 November 2017
3	Secondary identifying numbers: no
4	Sources of monetary or material support: Innovation Fund of the Federal Joint Committee (G-BA): VF16012
5	Primary sponsor: University Hospital Tübingen
6	Secondary sponsor(s): (to be found)
7	Contact for public queries: [name] med. [name], Geriatric Center of the University Hospital Tübingen; PD. Dr med. [name], Klinikum Stuttgart
8	Contact for scientific queries: [name] med. Dr phil. [name], Social and Preventive Medicine, Potsdam University
9	Public title: PAWEL: Patient safety, cost-effectiveness and quality of life: reduction of delirium risk and post-operative cognitive dysfunction after elective procedures in the elderly
10	Scientific title: see 9
11	Countries of recruitment: Germany, Baden-Wuerttemberg
12	Health condition(s) or problem(s) studied: delirium, postoperative cognitive dysfunction (POCD)
13	Intervention(s): trans-sectoral multimodal perioperative intervention for elective surgical interventions vs treatment as usual (TAU)
14	Key inclusion criteria: patients older than 70 years undergoing an elective surgery (heart, thorax, vessels, proximal big joints and spinal cord, genitourinary, gastrointestinal, and general elective surgery procedures) with at least 60-min duration of anesthesia (cut-to-suture time) Key exclusion criteria: emergency surgery, newly discovered severe dementia (red flag: Mini Mental State Examination (MMSE) < 15, Montreal Cognitive Assessment (MoCA) < 8) without caregiver holding power of attorney, 120 km of driving distance to the center, inability to consent due to decreased German language abilities, poor clinical prognosis (survival < 15 months)
15	Study type: stepped wedge cluster randomized design
16	Date of first enrolment: 20 November 2017
17	Target sample size: 1800 for the delirium risk score, 1500 thereof for comparison of intervention
18	Recruitment status: enrolling by invitation
19	Primary outcome(s): delirium prevalence, measured by daily delirium screening (I-Confusion Assessment Method-based scoring system for delirium severity (I-CAM-S)) over 7 days post surgery, as well as after 2 and 6 months; Nursing Delirium Screening Scale (NuDESC) on days 2 and 6 post surgery
20	Key secondary outcome(s): delirium duration as described in the primary outcome assessment. Prevalence of POCD 2 and 6 months after surgery as measured by a neuropsychological test battery (Montreal Cognitive Assessment (MoCA), digit span backwards and Trail Making Test A and B (TMT A and B)) as well as cognitive performance measured with the continuous nonstandardized test values of these scales. A cognitive deficit is defined as the presence of a test value ≤ 0.5 standard deviations, normalized for age, gender, and education, in one of these test procedures

### Trial overview

The consortium leader will manage the project, oversee the financial transfers, monitor the progress according to the planned schedule, and communicate with the study sponsor Innovationsfonds des Gemeinsamen Bundesausschusses. The consortium leader is also part of the steering committee, whose main tasks are dealing promptly with the everyday project issues, monitoring the recruitment progress and the implementation of the intervention modules, and managing the study documentation. The members of the steering committee are also part of the project committee, which includes two members from each study site. The project committee accompanies the study and coordinates the joint publications as well as the requests for data analysis. If necessary, the project committee, based on interim analyses performed every 3 months, can decide on early termination of the project. Moreover, in its meetings every 6 months, the committee may deal with any relevant project issues. An international scientific advisory board of well-established professionals, including a geriatrician, an anesthetist, a gerontologist, and a delirium expert, ensures the scientific quality of the trial. The advisory board is comprised of four delirium and POCD experts. An external Regional Ethics and Data Monitoring Board (REDMB) includes national experts on delirium and POCD who are independent of the sponsor and trial investigators, and have no competing interests. They may be called upon to deal with ethically difficult issues, and they will also act as a monitoring board for adverse events (AEs). Furthermore, if the trial was to terminate early, the REDMB would take part in that decision.

### Participants

#### Inclusion criteria

Eligible patients are aged 70 years or older and scheduled for elective surgery (cardiac, thorax, vessels, proximal large joints or spine, genitourinary, abdominal, or general elective surgery procedures) with a planned duration of surgery of at least 60 min (cut-to-suture time) under general, spinal, or regional anesthesia. As delirium is a high risk in dementia and frailty, we include patients with dementia or frailty who can consent to the trial or whose substitute decision-makers provide consent. 

#### Exclusion criteria

Patients undergoing emergency surgery procedures, patients unable to consent due to insufficient mastery of the German language or with newly discovered severe dementia (red flag: Mini Mental State Examination (MMSE) < 15, Montreal Cognitive Assessment (MoCA) < 8) without a substitute decision-maker, patients with a poor clinical prognosis (expected survival of less than 15 months), and patients who have a long driving distance to the study site (> 120 km) are to be excluded from the trial.

The recruitment procedure is described in Fig. 2. Patients who are not able to consent may also be recruited if the legal guardian consents to the patient’s study participation, given that such patients are especially at risk of developing delirium and POCD after surgery [10], and they could eminently benefit from the intervention.

**Fig. 2 Fig2:**
[figure not shown]
Recruitment procedure. PAWEL Patient safety, cost-effectiveness and quality of life: reduction of delirium risk and post-operative cognitive dysfunction after elective procedures in the elderly

